### Data collection and management

All the study-related data of recruited patients will be recorded in an electronic storage system. These data will include baseline information, intraoperative and postoperative follow-up information, and lung ultrasound-related data. The data of each patient will be entered into the EpiData database using a dual data entry system. The data will not be disclosed to other researchers until the study is completed. An inspector will regularly check and revise these records to ensure data quality.

### Interventions

Patients will be intravenously infused with the label-covered trial agent 5 min before induction, and all patients will undergo a standardized general anesthesia and analgesia protocol. Lung ultrasound scans will be performed at three points in each patient: immediately after radial artery puncture (T1), 15 min after tracheal intubation (T2), and before extubation (T3). Three arterial blood samples will be obtained through radial artery puncture at each time point (T1, T2, T3), and blood gas measurements will be performed immediately using a standard technique (ABL800).

Agent preparation method: S-ketamine group (group 1): S-ketamine (50 mg; 2 mL) will be diluted with normal saline to 5 mL in an opaque 5-mL syringe (10 mg mL^−1^). Normal saline group (group 2): 5 mL of normal saline. Both will be labeled as “study agents” and injected with a dose of 0.025 mL kg^−1^.

### Anesthesia and analgesia

Standard monitoring of non-invasive blood pressure (BP), heart rate (HR), and pulse oxygen saturation (SpO_2_) will be commenced upon the patient’s arrival at the operating room. Radial artery puncture will be performed under local anesthesia to perform blood gas sampling and invasive arterial blood pressure (ABP) monitoring. Patients will receive midazolam 2 mg intravenously as a premedication 5 min before induction. Anesthesia will be induced by pre-oxygenation with 100% oxygen inhalation for 3 min via a face mask. This will be followed by an intravenous administration of sufentanil 0.3–0.5 μg kg^−1^, propofol 1.5–2.5 mg kg^−1^, and rocuronium 0.6–1.0 mg kg^−1^. After spontaneous breathing disappears, the volume control mode will be used to control the patient’s breathing through the mask for 2 min, with a tidal volume of 6–8 mL kg^−1^ (predicted body weight without PEEP), ventilatory frequency of 12 bpm, and 100% oxygen concentration. It takes approximately 5–7 min from pre-oxygenation to start intubation, and then we intubate with a suitably sized tracheal tube with a cuff. All patients will receive mechanical ventilation with a FiO_2_ of 0.4 and an inspiratory-to-expiratory ratio of 1:1.5–2. The ventilatory parameters will be adjusted to maintain the end-tidal carbon dioxide partial pressure (P_ET_CO_2_) within 35–40 mmHg and airway pressure not exceeding 25 cm H_2_O.

Anesthesia will be maintained with continuous intravenous infusion of remifentanil 0.1–0.2 μg kg^−1^ min^−1^ and propofol 3–6 mg kg^−1^ h^−1^, combined with inhalation of 0.5–2 MAC sevoflurane. Sufentanil 0.05–0.1 µg kg^−1^ will be administered intermittently in accordance with the demand for analgesia. The mean arterial pressure and HR will be maintained within 30% of the baseline value. The patient’s axillary temperature will be maintained at 36–37 °C throughout the operation. During anesthesia, ABP, P_ET_CO_2_, peak inspiratory pressure (PIP), and plateau pressure (P_plat_) will be monitored. All anesthetics will be discontinued at the end of the surgery.

### Pulmonary ultrasonography

A well-trained blinded anesthesiologist will perform all lung ultrasound scans using SonoSite M-Turbo with a 5–12-MHz linear transducer. Patients will be scanned in the supine position following the lung ultrasound method described by Sun et al. [37]. Briefly, six regions will be scanned in each hemithorax. Scans 1 and 2 will be performed in the clavicle midline, scans 3 and 4 will be performed in the axillary midline, and the intercostal scans (scans 5 and 6) will be performed at the fifth and sixth intercostal spaces in the posterior axillary line. A linear probe will be placed parallel to the ribs, and the intercostal space of each region will be scanned sequentially from right to left, cranial to caudal, and anterior to posterior within 2 min.

The video clips of each region will be stored on a portable hard drive for offline analysis. Scoring criteria of B-lines are as follows: B-lines will be categorized into four grades (0–3): B0, normally ventilated areas with lung sliding sign: A-line and isolated B-lines (< 3); B1, mild reduction in lung ventilation/moderate loss of lung tissue gasification: B-lines (≥ 3) with clear boundary, regular distribution, and spacing ≥ 7 mm, or irregular, clear interval; B2, severe reduction in lung ventilation/severe lung gasification: multiple coalescent B-lines spaced ≤ 3 mm and continuous fusion; and B3, atelectasis/pulmonary consolidation: tissue-like signs, fragment signs, and bronchial inflation signs appear.

### Outcome measurement

#### Primary outcome

Total LUS at T2.

#### Secondary outcomes

LUS in 12 chest regions (scans 1-6 in each hemihorax) at T2; total LUS at T3; arterial blood gas analysis results (PaCO_2_, PaO_2_) and PaO_2_/FiO_2_ at T2 and T3, P_plat_ and dynamic lung compliance (Cdyn) [Cdyn = tidal volume/(PIP-PEEP)] at T2 and T3; the incidence of postoperative complications associated with S-ketamine at 2 h and 24 h after surgery (visual impairment, dizziness, pathological irritability, nightmares, and hallucinations); the incidence of PPCs at 2h and 24 h after surgery (the clinical outcome definitions of PPCs will adopt European joint taskforce guidelines published in 2015 [38]. These include respiratory infection, respiratory failure, atelectasis, pleural effusion, pneumothorax, bronchospasm, aspiration pneumonia, pulmonary edema, ARDS, tracheobronchitis, pulmonary edema, exacerbation of pre-existing lung disease, pulmonary embolism).

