#### Other indicators to be recorded

Baseline value

General information of patients: age, height, weight, BMI, smoking history, ASA, type of operation, complications, types, and severity of complications.

Anesthesia-related variables: duration of apnea during artificial airway establishment (recorded by stopwatch), laryngoscope insertion times, liquid volume (from entering the room to T2).

Intraoperative indicators: total LUS at T1; arterial blood gas analysis results (PaCO_2_, PaO_2_) and PaO_2_/FiO_2_ at T1; mechanical ventilation parameters (tidal volume, ventilation frequency, and FiO_2_).

(2)Other indicators

Vital signs (pulse, BP, HR, and SpO_2_) at each time point (T1, T2, and T3).

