### Sample size calculation and statistical analysis

According to previous studies, the incidence of atelectasis is approximately 90% in patients pre-oxygenated with 100% oxygen within a few minutes after anesthesia [1, 4, 33, 39]. We estimate that the incidence of atelectasis is 85%, and the preoperative administration of S-ketamine can reduce the incidence of atelectasis to 60%. The sample size was calculated by PASS 15.0. Finally, 50 cases in each group will be estimated to provide 80% power with a significance level *α* of 0.05, allowing for a dropout rate of 5%.

Statistical analysis will be performed using SPSS 24.0. Values will be expressed as mean ± standard deviation ($$\overline{x }$$±s), median and interquartile range (IQR), and percentages according to different distribution types. After testing for normality of continuous variables, Student’s *t*-test or the Mann–Whitney *U*-test will be used for comparison between and within groups, as appropriate. Categorical variables will be analyzed using the chi-square test or Fisher’s exact test. All statistical analyses in our study will be conducted with a bilateral test, and statistical significance will be set at *P* < 0.05. We will exclude patients whose primary data are missing. Both intention-to-treat analysis and per-protocol analysis will be conducted in this study.

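### Cdyn is compared as an absolute value with no covariate, so any variation with body size stays in the error term; adjusting for recorded height would recover some precision on this secondary outcome

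*Protocol article*

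**What the plan says.** - **Definition and timing** (Protocol article, Secondary outcomes): "dynamic lung compliance (Cdyn) [Cdyn = tidal volume/(PIP-PEEP)] at T2 and T3". The value is not divided by any measure of body size. Table 1 marks it at T2 and T3 only.
- **Test** (Sample size calculation and statistical analysis): after a normality check, a t-test or Mann–Whitney test "will be used for comparison between and within groups". No covariate is named.
- **Time points** (Interventions): "immediately after radial artery puncture (T1), 15 min after tracheal intubation (T2), and before extubation (T3". T1 falls before intubation.
- **What T1 contains** (Other indicators to be recorded): "Intraoperative indicators: total LUS at T1; arterial blood gas analysis results". No lung-mechanics variable is listed there.
- **Body size on record** (same section): "General information of patients: age, height, weight, BMI, smoking history, ASA, type of operation". Height is listed and sex is not.
- **Who can enter** (Inclusion and Exclusion criteria): urological, obstetric and gynecological patients. BMI is capped, but height and sex are not restricted.
- **Use of predicted body weight** (Anesthesia and analgesia): the tidal volume for mask ventilation is set per kilogram of "predicted body weight without PEEP".

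**The concern.** If larger patients have larger absolute compliance, part of the spread in Cdyn reflects stature and not treatment. For lung ultrasound score and blood gases, a T1 value is available that could absorb stable differences between patients. For Cdyn there is none, so only a body-size covariate can do this, and the stated tests use none. Cdyn and plateau pressure are the only lung-mechanics outcomes in the trial, and they bear on the airway-relaxation rationale in the Background. At stake is how small a difference in Cdyn the trial can resolve. The primary outcome and the sample size are not affected.

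**Working it through.** **1. The plan's own figure.** The only sample-size figure concerns binary atelectasis: 85% against 60%, two-sided 0.05, 80% power. With unpooled variance, n = (1.96 + 0.84)² × (0.85×0.15 + 0.60×0.40) / 0.25² = 7.85 × 0.3675 / 0.0625 = 46.2, so 47 per arm. Dividing by 0.95 for dropout gives 49.5, so 50. The stated 50 per group is reproduced. The article gives no figure for Cdyn, so the rest takes 50 per arm as given.

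**2. What 50 per arm resolves without adjustment.** The detectable difference at 80% power is 2.80 × √(2/50) = 0.56 standard deviations of raw Cdyn.

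**3. Assumptions for body size (none are in the documents).** Heights are 160 ± 6 cm in women and 172 ± 6 cm in men, with 0–50% men. Predicted body weight is 45.5 kg (women) or 50 kg (men) + 0.91 × (height − 152.4). The size-free part of compliance has a coefficient of variation (CV) of 0.20–0.30. By simulation, the CV of predicted body weight is then 0.104–0.157.

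**4. Share of variance if compliance is proportional to predicted body weight.** CV²(raw) = CV²(size) + CV²(size-free) + their product, and R² = CV²(size) / CV²(raw).
- Low end (0.104 and 0.30): 0.0108 + 0.0900 + 0.0010 = 0.1018, so R² = 0.0108 / 0.1018 = 0.11.
- High end (0.157 and 0.20): 0.0246 + 0.0400 + 0.0010 = 0.0656, so R² = 0.0246 / 0.0656 = 0.38.

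**5. Weaker scaling.** If compliance follows the square root of predicted body weight, R² is about 0.03–0.14. With no scaling it is 0.

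**6. Gain from regression adjustment.** The standard error is multiplied by √(1−R²), and the equivalent sample size is 50/(1−R²).

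| Scaling assumed | R² | SE factor | Equivalent n per arm | Detectable difference (raw SD) |
|---|---|---|---|---|
| Proportional | 0.11–0.38 | 0.94–0.79 | 56–81 | 0.53–0.44 |
| Half | 0.03–0.14 | 0.98–0.93 | 52–58 | 0.55–0.52 |
| None | 0 | 1.00 | 50 | 0.56 |

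**7. Height alone.** In the same simulation with proportional scaling, height by itself gives R² of 0.11–0.37, against 0.11–0.38 for predicted body weight. The recorded variable captures nearly all the gain.

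**8. Dividing by predicted body weight instead.** The ratio of relative variances, raw over divided, is 1.13–1.64 under proportional scaling, about 1.0 under half scaling and 0.59–0.88 under no scaling. Below 1, division makes the comparison less precise. Regression estimates the slope from the data and so does not over-correct in this way.

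**The case against.** The strongest reply is that nothing here is invalid. An unadjusted comparison of a randomised secondary outcome is unbiased and keeps its error rate. No power is claimed for Cdyn, and covariates are often left to an analysis plan. Validity is conceded in full. What remains is that the article does write down both the formula and the family of tests, and for this variable that stated choice gives up precision that a recorded covariate could return.

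The gain also rests entirely on assumptions. The male share is unknown, and two of the three surgical fields enrol women. With no men and proportional scaling, R² is only 0.11–0.21. This stands, and is why the range runs down to zero.

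A reader might infer four stronger points that the documents do not support:
- **That a T1 measurement was forgotten.** T1 precedes induction and intubation, so no ventilator compliance exists then.
- **That tidal volume set by predicted body weight makes Cdyn rise with size.** Cdyn is a ratio, and a larger volume with a proportionally larger pressure leaves it unchanged. What matters is whether compliance itself scales with size, on which the documents are silent. The rule is also stated for mask ventilation ("predicted body weight without PEEP), ventilatory frequency of 12 bpm"), before Cdyn is measured.
- **That chance imbalance in size biases the comparison.** Under the assumptions above, the arm difference in mean predicted body weight has a standard error of 0.104 × √(2/50) to 0.157 × √(2/50), about 2–3%. The test's error rate already allows for this.
- **That predicted body weight can be computed from the listed data.** It needs sex, which is not in the list.

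**Conclusion.** The point holds as a minor matter of efficiency. Cdyn is an absolute value tested without a covariate, so any variation with body size remains in the residual, and no baseline can remove it. The consequence is a loss of precision on a secondary outcome. It does not amount to bias, and it does not support saying that a real difference in lung mechanics would be hidden. Under proportional scaling, the detectable difference would fall from 0.56 to 0.53–0.44 standard deviations with adjustment. Under half scaling it would fall to 0.55–0.52, and with no scaling it would not change. These ranges depend on the assumed heights, sex mix and size-free variability, none of which the documents give.

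**What to change.** In the statistical analysis section, state that Cdyn at T2 and at T3 will each be compared by a linear model on group and recorded height, adding sex where it is available. Keep raw Cdyn by group in the tables. Fix the scale of the model (raw or log) in advance, because the normality-driven choice of test would no longer apply to this variable. Do not replace the outcome by Cdyn divided by predicted body weight.

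The cost is one line of analysis wording and one degree of freedom for height, with one more if sex is added. Height is already recorded, so no new measurement and no additional patients are needed.

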#### Other indicators to be recorded

Baseline value

General information of patients: age, height, weight, BMI, smoking history, ASA, type of operation, complications, types, and severity of complications.

Anesthesia-related variables: duration of apnea during artificial airway establishment (recorded by stopwatch), laryngoscope insertion times, liquid volume (from entering the room to T2).

Intraoperative indicators: total LUS at T1; arterial blood gas analysis results (PaCO_2_, PaO_2_) and PaO_2_/FiO_2_ at T1; mechanical ventilation parameters (tidal volume, ventilation frequency, and FiO_2_).

(2)Other indicators

Vital signs (pulse, BP, HR, and SpO_2_) at each time point (T1, T2, and T3).

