	**Study period**						
	Enrollment	Allocation	Postallocation				
Time point	Day − 1	Day 0	T1 (after radial artery puncture)	15 min after intubation (T2)	Before extubation (T3)	2 h after surgery	24 h after surgery
Enrollment							
Eligibility screen	X						
Informed consent	X						
Randomization		X					
Allocation		X					
Interventions							
[Group 1] S-ketamine group			X				
[Group 2] Normal saline group			X				
Outcome assessment							
Total LUS			X	※	X		
LUS of 12 chest regions				X			
PaCO_2_, PaO_2_, and PaO_2_/FiO_2_			X	X	X		
P_plat_ and Cdyn				X	X		
Incidence of postoperative complications associated S-ketamine						X	X
Incidence of PPCs						X	X

*LUS* lung ultrasound scores, *P*_*plat*_ plateau pressure, *Cdyn* dynamic lung compliance, *PPCs* postoperative pulmonary complications. ※ primary outcome

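### The T1 baseline has no role in the stated between-group comparison of lung ultrasound score (LUS) and blood gases, and a normality test on the trial's own data decides whether the primary result compares means or ranks

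*Protocol article*

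**What the plan says.** The primary outcome is "Total LUS at T2" (Protocol article, Primary outcome). The Interventions section schedules a lung scan and an arterial sample in each patient at T1, T2 and T3. Under Other indicators to be recorded, within the baseline block, the T1 results appear as "Intraoperative indicators: total LUS at T1; arterial blood gas analysis results" together with PaO2/FiO2.

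The analysis rule is in Sample size calculation and statistical analysis. It begins "After testing for normality of continuous variables" and then names Student's t-test or the Mann–Whitney U-test, which "will be used for comparison between and within groups, as appropriate". Summaries are mean with SD, median with IQR, "and percentages according to different distribution types". No covariate or adjusted model is named.

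On the order of events, the Interventions section says "Patients will be intravenously infused with the label-covered trial agent 5 min before induction" and places T1 just after radial artery puncture. It does not say whether the T1 scan and sample come before or after that injection. Table 1 marks both study agents in the T1 column.

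**The concern.** Two features of the stated analysis could be improved using data the trial already plans to collect.

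First, the T1 total LUS is the same measurement as the primary outcome, taken earlier in the same patient. A comparison of T2 values that ignores it leaves in the error term any between-patient variation that T1 would explain, and makes no allowance for a chance difference between arms at T1. The same holds for total LUS at T3 and for PaO2, PaCO2 and PaO2/FiO2.

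Second, the t-test and the Mann–Whitney test answer different questions, one about means and one about ranks. If a normality test chooses between them after the data are in, then the primary hypothesis, the summary and the effect estimate that goes with it are settled by the data. Total LUS is a bounded sum of 12 regional grades of 0 to 3, so it runs from 0 to 36, and the result of a normality test cannot be predicted with confidence.

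**Working it through.** **1. The plan's own sample size.** Inputs: 85% versus 60%, two-sided 0.05, 80% power, 5% dropout. With unpooled variance, n = (1.960 + 0.842)² × (0.85×0.15 + 0.60×0.40) / 0.25² = 7.849 × 0.3675 / 0.0625 = 46.2, so 47 per arm; 47/0.95 = 49.5, so 50 per arm. This matches the stated 50. The pooled-variance form gives 49, then 52. The figure rests on a binary incidence, so it neither supports nor limits what follows. It does give the number evaluable: 50 × 0.95 = 47.5, taken as 47 per arm.

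**2. Precision from adjusting for T1.** With correlation r between T1 and T2, adjustment multiplies the residual variance by 1 − r². The documents give neither r nor an SD, so r is an assumption shown over a range. By normal approximation, the difference detectable with 80% power at 47 per arm without adjustment is (1.960 + 0.842) × √(2/47) = 0.578 SD. With adjustment it is 0.578 × √(1 − r²). The power column holds the true difference at 0.578 SD.

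| r (assumed) | Variance factor 1 − r² | Variance saved | Detectable difference (SD) | Power at 0.578 SD | Equivalent n per arm, 47/(1 − r²) |
|---|---|---|---|---|---|
| 0 | 1.00 | 0% | 0.578 | 80.0% | 47.0 |
| 0.1 | 0.99 | 1% | 0.575 | 80.4% | 47.5 |
| 0.2 | 0.96 | 4% | 0.566 | 81.6% | 49.0 |
| 0.3 | 0.91 | 9% | 0.551 | 83.6% | 51.6 |
| 0.5 | 0.75 | 25% | 0.500 | 89.9% | 62.7 |
| 0.7 | 0.51 | 49% | 0.413 | 97.5% | 92.2 |

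**3. Chance imbalance at T1.** The standard error of the T1 difference between arms is √(2/47) = 0.206 SD. A one-standard-error imbalance moves the unadjusted T2 difference by r × 0.206 SD: 0.02 SD at r = 0.1 and 0.10 SD at r = 0.5. The latter is 0.103/0.578 = 18% of the detectable difference.

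**4. The normality gate.** Simulation with 47 per arm, 3,000 runs per setting and the same distribution in both arms. A Shapiro–Wilk test was applied in each arm at 0.05, followed by the t-test if both arms passed and Mann–Whitney otherwise. The distributions are assumptions (scores on 0 to 36, mean about 7), and so is the choice of normality test, because the article names none.

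| Assumed shape | Runs switched to Mann–Whitney | Type I error of the two-step rule |
|---|---|---|
| Near-symmetric | 47% | 5.2% |
| Mild skew | 66% | 5.5% |
| Marked skew | 91% | 5.2% |

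The test used does depend on the sample drawn. The error rate stays close to 5%.

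**The case against.** The strongest reply is that an unadjusted two-sample comparison in a 1:1 randomised trial is valid. It is unbiased over randomisation, and its type I error already allows for chance imbalance. Adjustment would improve the analysis rather than correct an error, and a separate analysis plan could still add it. All of that stands. What the reply does not cover is the selection rule: the article does not leave the primary test open but states that the data will choose it. A later plan that followed this text would inherit the rule.

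Three stronger readings are tempting, and the documents do not support them:

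- **That the T1 data are left out of the analysis altogether.** The article also plans comparisons within groups, which may use T1, and the Discussion says gases are taken at three time points to study gas exchange. What can be said is that T1 has no stated role in comparing the arms; a change within one arm does not compare the arms.
- **That substantial precision is being thrown away on the primary outcome.** No correlation is given. Patients are ASA I–II, and those with abnormal chest imaging are excluded, so T1 LUS may sit near zero with little spread to adjust on. The gain could be 1% to 4% of variance. Whether blood gases would gain more is unknown, and they are secondary outcomes.
- **That the normality gate inflates false positives.** The simulation shows no material inflation.

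A further objection is that T1 might not be a pre-treatment value. This also stands, as a condition on the remedy: if any T1 scan or sample followed the injection, adjusting for it could remove part of the treatment effect.

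**Conclusion.** The point holds as a modest matter of efficiency and pre-specification, and the change should be made. The firm part comes directly from the text: a data-driven rule decides whether the primary result concerns means or ranks, so the effect measure is not fixed in advance. That justifies the change even if r is close to zero. The precision part is conditional. It runs from 1% of variance at r = 0.1 to 49% at r = 0.7, with the low end plausible for LUS, and every value of r is an assumption. The stated tests remain valid and the stated sample size is unaffected. Using T1 as a covariate depends on its having been measured before the study agent was given, which the article does not establish.

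**What to change.** Before unblinding:

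1. Define the primary analysis as a linear regression (ANCOVA with robust standard errors) of total LUS at T2 on arm, with T1 total LUS as covariate. Report the adjusted mean difference with its 95% CI.
2. Drop the normality test as a gate and keep the Mann–Whitney test as a pre-stated sensitivity analysis.
3. Use the same form for total LUS at T3 and for PaO2, PaCO2 and PaO2/FiO2 at T2 and T3, each with its own T1 value. Plateau pressure and compliance have no T1 measurement in Table 1, so this does not apply to them.
4. Reconcile the Interventions section and Table 1 on the order of the T1 scan, the T1 sample and the study injection. Use T1 as a covariate only where the scan and sample came before the injection.

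The cost is wording in the analysis section, plus a check of the recorded times for item 4. No new measurements or patients are needed.
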